# High dose oral and intravenous rifampicin for improved survival from adult tuberculous meningitis: a phase II open-label randomised controlled trial (the RifT study)

**DOI:** 10.12688/wellcomeopenres.14691.1

**Published:** 2018-07-10

**Keywords:** TBM, Tuberculous Meningitis, TB, rifampicin, Ultra, HIV

## Abstract

**Background**: Tuberculous meningitis (TBM) has 44% (95%CI 35-52%) in-hospital mortality with standard therapy in Uganda. Rifampicin, the cornerstone of TB therapy, has 70% oral bioavailability and ~10-20% cerebrospinal fluid (CSF) penetration.  With current WHO-recommended TB treatment containing 8-12mg/kg rifampicin, CSF rifampicin exposures frequently fall below the minimal inhibitory concentration for
*M. tuberculosis*. Two Indonesian phase II studies, the first investigating intravenous rifampicin 600mg and the second oral rifampicin ~30mg/kg, found the interventions were safe and resulted in significantly increased CSF rifampicin exposures and a reduction in 6-month mortality in the investigational arms. Whether such improvements can be replicated in an HIV-positive population remains to be determined.

**Protocol**: We will perform a phase II, open-label randomised controlled trial, comparing higher-dose oral and intravenous rifampicin with current standard of care in a predominantly HIV-positive population. Participants will be allocated to one of three parallel arms (I:I:I): (i) intravenous rifampicin 20mg/kg for 2-weeks followed by oral rifampicin 35mg/kg for 6-weeks; (ii) oral rifampicin 35mg/kg for 8-weeks; (iii) standard of care, oral rifampicin 10mg/kg/day for 8-weeks. Primary endpoints will be: (i) pharmacokinetic parameters in plasma and CSF; (ii) safety. We will also examine the effect of higher-dose rifampicin on survival time, neurological outcomes and incidence of immune reconstitution inflammatory syndrome. We will enrol 60 adults with suspected TBM, from two hospitals in Uganda, with follow-up to 6 months post-enrolment.

**Discussion**: HIV co-infection affects the bioavailability of rifampicin in the initial days of therapy, risk of drug toxicity and drug interactions, and ultimately mortality from TBM. Our study aims to demonstrate, in a predominantly HIV-positive population, the safety and pharmacokinetic superiority of one or both investigational arms compared to current standard of care. The most favourable dose may ultimately be taken forward into an adequately powered phase III trial.

**Trial registration**:
 ISRCTN42218549 (24
^th^ April 2018)

## Introduction

### Background

Worldwide, 10.4 million people are estimated to have fallen ill with Tuberculosis (TB) in 2016, resulting in 1.3 million deaths, and an additional 374,000 TB deaths in people living with HIV
^1^. The African region carries the greatest burden relative to its population; 281 cases for every 100,000 people, more than double the global average of 133 per 100,000. Additionally, of the 1.2 million HIV-infected people who developed TB worldwide, 74% were in the African World Health Organisation (WHO) region
^2^.

The true incidence of TB meningitis is not known due to lack of accurate diagnostics and scarce epidemiological data in many TB endemic regions. Central nervous system (CNS) TB accounts for ~1% of notified TB cases in Germany and the USA, but this proportion is likely to be significantly higher in HIV endemic regions where TB frequently manifests as disseminated disease
^3,
4^. As such, in the wake of the HIV epidemic; TB meningitis (TBM) is one of the leading causes of meningitis in both adults and children in Africa
^5,
6^. It is estimated there is likely to be well over 100,000 cases annually worldwide.

### Prognosis of TBM

TBM, the most devastating form of TB, is associated with a mortality of 7–28% of HIV-uninfected
^7^, and 29–63% of HIV-infected patients
^8,
9^. The driver of this 2 to 3-fold increased risk of death in HIV co-infection has not yet been elucidated. Neuro-disability is seen in up to 50% of survivors, regardless of their HIV serostatus. TBM cases account for up to 19% of all hospitalized HIV-associated TB cases and pose a significant challenge to healthcare services and care-givers, often requiring prolonged hospital stays and long rehabilitation periods
^10^. Delays in seeking medical care, diagnosis, and initiation of treatment are contributing factors to the high morbidity and mortality, particularly in resource-limited settings.

### Clinical TBM management

Early treatment with anti-tuberculous therapy and adjunctive corticosteroids is the most effective way of reducing death and disability from TBM. However, currently morbidity and mortality remains unacceptably high
^5^. Whilst the 4
^th^ edition of the WHO treatment guidelines suggest substituting ethambutol with streptomycin during the intensive phase of treatment this has not been widely adopted for a number of reasons, and treatment for TBM does not differ from that of pulmonary TB, with rifampicin (R), isoniazid (H), pyrazinamide (Z) and ethambutol (E) given for two months (intensive phase) followed by rifampicin and isoniazid (continuation phase), except that continuation phase is prolonged to complete 9–12 months
^2,
11^.

Due to variable TB drug penetration across the blood-brain barrier and blood-cerebrospinal fluid (CSF) barrier, optimal treatment regimens for pulmonary TB may not be the most effective options for TBM. Inadequate CNS drug penetration may be an important contributory factor to the high early mortality in TBM
^12^. Improved early treatment outcomes may be achieved by altering drug selection, drug doses, and routes of administration to ensure adequate drug delivery to the site of disease and maximal early mycobactericidal activity in the CNS.

### Rifampicin in TBM

Rifampicin is the cornerstone drug in the treatment of TBM, as evidenced by the fact that those infected with rifampicin-resistant
*Mycobacterium tuberculosis* (
*M.tb*) strains have a near-universal fatal outcome, even with treatment with second-line drugs in resource-rich settings
^5,
13,
14^. Mortality is not nearly so high in patients with isoniazid mono-resistant TBM
^6^.

In addition to male sex and low body weight, which are associated with more rapid drug clearance
^15^, malabsorption may contribute to reduced systemic drug bioavailability in HIV-infected persons
^16–
21^. A recent comprehensive meta-analysis of rifampicin pharmacokinetics confirmed that during the initial days of TB treatment rifampicin total plasma exposure to rifampicin is reduced in HIV co-infected adults (AUC 37.2mg.h/L in HIV-positive versus 56.7mg.h/L in HIV-negative, p=0.003). Interestingly, this association did not persist in steady-state (>7 days on therapy, once saturation of first-pass metabolism and the establishment of metabolic autoinduction is well established)
^22^. Lower plasma levels of antituberculous agents are predictive of poorer outcomes in pulmonary TB
^23^, thus the lower plasma levels of rifampicin seen in HIV-positive individuals in the initial days of TBM therapy may be particularly relevant in TB meningitis, which carries a high early mortality. Specific factors that potentially play a role in reduced bioavailability include HIV-related enteric infections
^17,
18^, HIV-associated enteropathy and chronic intestinal immune activation affecting regulation of drug transporters. Patients with TBM often present while critically ill, are vomiting and frequently receive drugs through a nasogastric tube. Such factors may further associate with reduced TB drug concentrations, which could explain the lower plasma rifampicin concentrations observed in patients with TBM compared to those with pulmonary TB taking the same dose from the same setting
^24,
25^.

Rifampicin is largely protein bound and thus has limited CSF penetration, with reported CSF concentrations often reaching 10–20% of those in plasma
^25,
26^. Suggested target concentrations of rifampicin are >8mcg/ml at the site of disease, but CSF rifampicin concentrations seldom exceeded the minimum inhibitory concentration (MIC; 0.25mcg/ml) against
*M. tuberculosis* at the standard oral adult dose (8–12mg/kg)
^12^. Currently, little is known about rifampicin concentrations in brain matter, spinal cord or meninges and how plasma levels or inflammation affect tissue concentrations.

The evidence for the currently recommended dose of rifampicin (10mg/kg/day) in TBM treatment is scant, and this dose falls on the steep part of the dose-response curve for sterilising effect
^27^. Recent studies by the Pan-African Consortium for the Evaluation of Antituberculous Antibiotics in pulmonary TB have shown that rifampicin dosed at 35mg/kg is associated with improved early bactericidal activity and 2-fold faster rate of sputum conversion (Hazard Ratio 1.99, 95% CI:1.21-3.29) as compared to standard therapy. Furthermore, this dose was safe and well tolerated, with a 14% grade 3-5 adverse event incidence as compared with 10% with standard 4-drug TB therapy with rifampicin dosed at 10mg/kg
^28^.

Ruslami
*et al*. investigated the safety and pharmacokinetic (PK) profiles of higher than normal dose
*intravenous* (IV) rifampicin as well as oral moxifloxacin in adults with TBM. Although not powered to detect a mortality benefit, improved survival was observed in patients receiving 600mg IV rifampicin (~13mg/kg/day) compared to the oral standard dose (~10mg/kg/day). Patients who received IV rifampicin had a more rapid resolution of coma (4 versus 5 days), reduced mortality at 8-weeks (24% versus 55%) and 6-months (34% versus 65%); (adjusted Hazard Ratio=0.42; 95% CI 0.20-0.91, p=0.03) compared with those who received oral standard dose rifampicin. The change in rifampicin dose and mode of delivery was associated with a 3-fold increase in plasma area under the time-concentration curve (AUC) and maximum concentration (C
_max_) and a 3-fold increase in CSF C
_max_ from 0.21 to 0.60 mcg/mL.

A second phase II study in Indonesia evaluating increased
*oral* doses of 30mg/kg or 20mg/kg versus standard of care (10mg/kg) also reported no increase in toxicity in the high dose arms and CSF C
_max_ was significantly increased (25.5 mg/L [11.9 to 55.5], 18.1 mg/L [2 to 43.6], 7.2 mg/L [2.2 to 14.1] respectively, <0.001). In those with microbiologically confirmed TBM there was a trend towards lower 6-month mortality in the 30mg/kg arm compared to standard of care (7% versus 36% (HR 0.16 [0.02 to 1.34], p=0.09)
^29^.

In contrast, a large Vietnamese trial of an intensified TBM treatment containing oral rifampicin 15mg/kg/day versus standard of care showed no differential effect on mortality (27.7% versus 27.9%, hazard ratio 0.94; 95%CI 0.73 to 1.22; p=0.66)
^30^

The conflicting evidence from prior trials evaluating the benefits of higher than standard doses of rifampicin for TBM creates a situation of equipoise that can only be answered with an adequately powered phase III trial examining a rifampicin dose with proven pharmacokinetic-pharmacodynamic superiority to the standard of care. This phase II study aims to demonstrate pharmacokinetic superiority of one or both of the investigational arms so that the most favourable dose may ultimately be taken forward into a phase III study. Additionally, it is important to generate PK and safety data from HIV-positive African adults, as HIV co-infection can have a significant impact on TBM outcomes, pharmacokinetics and drug toxicity.

## Protocol

This is version 1.2.1, 19
^th^ February 2018.

### Hypotheses

Our
**primary hypothesis** is that intravenous rifampicin (20mg/kg) and high dose oral rifampicin (35mg/kg) will result in significantly increased plasma and CSF exposure during the critical early days of TBM treatment as compared to standard control (10mg/kg oral rifampicin).

Our
**secondary hypotheses** are that high dose rifampicin will lead to improved early mycobacterial clearance from the CNS, reduced inflammatory response, and thereby will result in more rapid resolution of coma, improved long-term functional status, reduced TBM immune reconstitution inflammatory syndrome (IRIS) incidence and lower mortality.

### Main study objectives

***Primary objective***. Our primary objective is to determine whether higher-dose rifampicin, delivered either orally at 35mg/kg/day or intravenously at 20 mg/kg/day for 2-weeks (followed by orally at 35 mg/kg/day for 6-weeks) is safe and provides exposure profiles that are favourable compared to the 10 mg/kg standard dose oral rifampicin.

***Secondary objectives***. Our secondary objectives are to observe whether greater rifampicin exposure in CSF is associated with any clinical benefit including more rapid resolution of coma, improved long-term functional status, reduced TBM-IRIS incidence and lower mortality.

### Ancillary studies

Two ancillary studies will be conducted within the RifT trial, the second of which will only take place at Mulago Hospital.

***Evaluation of the diagnostic accuracy of Xpert MTB/Rif Ultra (Ultra) in TBM***. Our hypothesis is that CSF Ultra is significantly more sensitive than CSF Xpert MTB/Rif or culture in the diagnosis of TBM.

***Descriptive study of brain tissue rifampicin concentrations on autopsy specimens***. Our hypothesis is that brain tissue concentrations will correlate with plasma and CSF concentration and will be significantly higher in the investigational arms.

### Design and setting

RifT is a three arm, parallel group, phase II open label randomised controlled trial (see
Figure 1), evaluating three rifampicin regimens over an 8-week intervention period, as follows:

A. Intravenous 20mg/kg/day rifampicin for 2-weeks (followed by oral rifampicin 35mg/kg/day for 6-weeks)B. Oral 35mg/kg/day rifampicin for 8-weeksC. Standard of care oral rifampicin (~10mg/kg/day) for 8-weeks

**Figure 1. f1:**
[figure not shown]
Study flow chart.

All participants will receive a standard backbone of oral TB treatment (consisting of isoniazid ~5mg/kg/day, pyrazinamide ~25mg/kg/day, ethambutol ~20mg/kg/day) and daily IV dexamethasone (0.4mg/kg/day) for 1 week then weaned over a 6–8 week period, as per WHO guidelines.

The trial will be set in two hospitals in Uganda: Mulago National Referral Hospital and Mbarara Regional Referral Hospital. The study population will be adults (≥18 years of age) with a diagnosis of TBM and treatment for TBM planned by the attending physician.

### Endpoints

***Primary end points***

*1. Pharmacokinetic parameters*

Plasma and CSF rifampicin area under the curve (AUC
_0-24h_), and maximum concentration (C
_max_)

*2. Adverse events*

We will use a composite safety endpoint for the 8-week intervention period that includes clinical grade 3-5 adverse events (AEs) (as classified by Division of AIDS (DAIDS) Toxicity Scale) or all serious adverse events (SAEs), drug-induced liver injury (DILI), grade 3-5 defined by alanine transaminase (ALT) >5x upper limit of normal (ULN), or discontinuation of rifampicin for >5 consecutive days in the first 8 weeks for any cause.

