**Control arm, standard of care arm (R10PO)**

The control arm will receive standard of care TB treatment: Oral rifampicin ~10 mg/kg, isoniazid ~5 mg/kg, pyrazinamide ~25 mg/kg, ethambutol ~20 mg/kg in fixed-dose combination tablets according to weight bands for 8 weeks (
Table 4). Participants will receive intact tablets or via nasogastric tube. Fixed dose combination antituberculous therapy will be prescribed through routine care pathways initially via the hospital and subsequently via at TB clinics according to National Guidelines.

***Pharmacokinetic sampling.*** Intensive plasma PK sampling will take place on day 2(+/-1) at hours 0, 2, 4 and 8 post dose as well as a single CSF sample. Where possible a single plasma and CSF sample will be collected on day 14 (+/- 2 days).

***Blood test monitoring.*** Routine blood monitoring will take place on days 1, 3, 7 and 14, week 4 and week 8 to monitor for any rifampicin-related toxicity (
Table 5 and
Table 6).

**Table 5. T5:** In-patient schedule of events.

Study visit	Screening	Enrolment D1	Day 2	Day 3	Day 7	Day 10	Day 14	Further Hospitalization
Visit window (days)			±1	±1	±1	±1	±2	
Screening Consent	X							
Assess eligibility criteria		X						
Informed enrolment consent		X						
Clinical history and examination								
Past medical history	(X)							
Medication review	(X)	X	X	X	X	X	X	X
Document HIV status	(X)							
Current symptoms	(X)	X	X	X	X	X	X	X
Examination	(X)	X	X	X	X	X	X	X
GCS score	(X)	X	X	X	X	X	X	X
BMRC disease grade		X	X	X	X	X	X	X
Adverse events assessment ^b^		X	X	X	X	X	X	X
Investigations								
HIV-test (if not known positive)	(X)							
Cryptococcal antigen	(X)							
Sodium/Potassium	X ^i^	X ^i^			X		X	X
Glucose (bedside)	(X)							
Creatinine ^h^	X ^i^	X ^i^			X		X	X
Hepatic panel ^a^	X ^i^	X ^i^		X	X		X	X
Blood Count (including differential)	X ^i^	X ^i^			X			X
CD4 count if HIV-positive	X ^i^	X ^i^						
Pregnancy test	Women							
CSF sample (aim >10ml, as per SOP ^c^)	(X)		X ^d^	as clinically indicated (storage of remaining specimen)			X (Paired plasma)	X (as clinically indicated)
Plasma PK sampling 0, 2, 4, 8 hrs			X					
Sparse plasma PK (one sample)							X	
Chest radiograph	(+/-)							
CT head ^f^	+/-	+/-						
Abdominal Ultrasound Scan		X						
Urine sample ^g^	(X)							
Blood/DNA/RNA storage		with consent						with consent
Approx. volume blood (mL)	0	20	20	3	7	0	7	7

**()**= part of routine medical care

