**^a^ Hepatic panel** = alanine aminotransferase (ALT), alkaline phosphatase (ALP) and bilirubin. Hepatitis BsAg, Hepatitis C Ab and INR will be added if baseline ALT is elevated. In the event of DILI hepatic panel will be performed more regularly.
**^b^ Adverse events** will be recorded according to DAIDS toxicity scale
**^c^ SOP** = standard operating procedure detailing exact processing and testing algorithm of CSF
**^d^ CSF PK** will be timing randomised to early (2–4hrs) or medium (4–6hrs) or late interval (6–8hrs) post dose.
**^f^ Contrast enhanced CT head** is indicated if there is focal neurology at baseline or during enrolment period
^g^
**Urine** sample may be collected for testing with LAM (lipoarobinmannan) or urine Xpert MTB/Rif Ultra as part of TB work-up
^h^ Additional
**renal monitoring** will be undertaken in those with abnormal baseline creatinine
^i^
**Baseline bloods** must occur at either screening or enrolment visit. It is likely these visits will be on the same day. If baseline bloods were done at screening and enrolment occurs >48 hours later baseline blood tests will be repeated.

**Table 6. T6:** Out-patient schedule of events.

Study visit	Week 4	Week 8	Week 12	Week 18	Week 24	Sick Visit
Visit window (weeks)	±1	±1	±1	±2	±2	As needed
Dispensing of study drug		X	standard fixed dose therapy til 12 months as per local guidelines			
Interim history	X	X	X	TELEPHONE CONSULTATION OR IN PERSON	X	X
Adverse events assessment	X	X	X		X	X
Medication review	X	X	X		X	X
Examination	X	X	X		X	X
Modified Rankin score		X			X	
Detailed neurocognitive follow-up		X			X	
Center for Epidemiological Studies of Depression Scale (CES-D)		X			X	
Sodium, potassium						X (if clinically indicated)
Creatinine						X (if clinically indicated)
Hepatic Panel ^a^	X	X				X (if clinically indicated)
FBC, differential ^b^						X (if clinically indicated)
Storage bloods ^c^		X				X (IRIS event only)
CSF with storage						X (if clinically indicated)
ART counselling ^d^	X	X				
Commence/switch ART ^d^		X				
Total volume of blood (ml)		20				20

^a^Hepatic panel = ALT, ALP, bilirubin +/- INR

^b^FBC; full/complete blood count

^c^Blood will be collected and stored for research if storage consent has been received, refer to site SOP.

^d^HIV-infected patients not receiving effective ART, ART counselling to be performed by qualified counsellors as per standard clinic procedures. Physician discretion allowed for timing of ART initiation.

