***Primary analysis***

**Pharmacokinetic analysis**

The following pharmacokinetic parameters will be calculated using standard two-stage approach involving calculation of pharmacokinetic parameters in those patients in whom a full PK curve was recorded:

1. C
_max_ - the peak concentration of the drug after administration2. T
_max_ - the time to reach C
_max_

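### The only stated primary PK method needs a full curve per patient, so it gives no CSF Cmax or CSF AUC0-24h from one day-2 CSF sample

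*Protocol article*

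**What the plan says.** - **Endpoint.** Under Primary end points, the first item is "Plasma and CSF rifampicin area under the curve" over 0 to 24 hours, together with Cmax. That is four quantities: AUC0-24h and Cmax, each in plasma and in CSF. The primary hypothesis likewise covers early exposure in both fluids.
- **Day-2 sampling.** The Pharmacokinetic sampling paragraph (Interventions) takes plasma "at hours 0, 2, 4 and 8 post dose as well as a single CSF sample".
- **Timing of the CSF sample.** Table 5, footnote d, says CSF PK "will be timing randomised to early (2–4hrs) or medium (4–6hrs) or late interval (6–8hrs) post dose".
- **Day 14.** "Where possible a single plasma and CSF sample will be collected on day 14", with a window of 2 days either side.
- **Method.** Under Primary analysis, Pharmacokinetic analysis, the parameters Cmax, Tmax, AUC0-24 and time above MIC come from a "standard two-stage approach involving calculation of pharmacokinetic parameters in those patients in whom a full PK curve was recorded". No separate rule is given for CSF.
- **Population model.** A population pharmacokinetic-pharmacodynamic model appears only under Secondary analysis, where it relates exposure to survival, recovery of consciousness and functional status.

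**The concern.** A two-stage analysis first derives each patient's own Cmax and AUC from that patient's serial concentrations, and then compares those values between arms. One CSF concentration supports neither: it is not an area, and nothing shows whether it is the peak. The method as written therefore does not fit the CSF data that the schedule collects.

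CSF exposure is the trial's rationale. It is part of the primary hypothesis and the basis of the secondary objectives, and the Discussion says that the pharmacokinetic results will guide the dose taken into phase III. With no usable CSF method fixed, someone in an open-label trial would have to choose one later: the raw concentration, naive pooling or a model. Those choices can give different answers on a primary endpoint.

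**Working it through.** **1. The plan's own figure.** The Sample size section gives 90% power with 15 per arm for a difference of 0.54 in log Cmax, SDs 0.36 and 0.48, two-sided alpha 0.05, unequal-variance t-test.

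- SE = √(0.36²/15 + 0.48²/15) = √(0.00864 + 0.01536) = √0.024 = 0.155
- Noncentrality = 0.54/0.155 = 3.49; Satterthwaite df = 26.0
- Power = 91.8%. With 14 per arm it is 89.8%, so 15 is the smallest number that reaches 90%.

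The figure reproduces and is not in dispute. The section does not say whether this Cmax is in plasma or CSF, so no power is shown specifically for a CSF quantity.

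**2. What the schedule supplies and what the method needs.**

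| | Plasma | CSF |
|---|---|---|
| Day-2 samples per participant | 4 (0, 2, 4, 8 h) | 1 (at a time within 2–8 h) |
| Day-14 samples per participant | at most 1 | at most 1 |
| Fewest points in one dosing interval for an individual AUC | 2 | 2 |
| Participants scheduled for serial samples in one interval | all | 0 of 60 |

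The day-14 sample comes about 12 days after day 2, so it cannot be joined to the day-2 point to make a curve. CSF taken when clinically indicated is not serial sampling either. CSF Cmax and CSF AUC0-24h, 2 of the 4 primary PK quantities, therefore have no evaluable participant under the stated method.

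**3. Time covered.** The three windows together run from 2 to 8 h: 8 − 2 = 6 h, and 6/24 = 25%. No day-2 CSF sample is planned in the other 24 − 6 = 18 h (75%), made up of 0–2 h and 8–24 h.

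**4. Samples per window.** With 60 participants allocated 1:1:1, each arm has about 20. 20/3 ≈ 6.7 per window per arm, or 15/3 = 5 if 15 per arm are analysable.

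*Illustration, assuming the effect and SDs of step 1 also hold for CSF.* An arm comparison inside a single window would have power of about 42% (n = 5), 51% (n = 6) or 58% (n = 7). A CSF comparison therefore has to combine the windows, with time after dose in the model.

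**5. A single sample against the true peak.** *Illustration with assumed one-compartment CSF profiles*, C(t) ∝ exp(−ke·t) − exp(−ka·t), tmax = ln(ka/ke)/(ka − ke). Entries are the sample as a percentage of the true peak.

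| ka, ke (per h) | tmax | 2–4 h | 4–6 h | 6–8 h |
|---|---|---|---|---|
| 0.5, 0.2 | 3.1 h | 93–100% | 77–96% | 56–77% |
| 0.3, 0.15 | 4.6 h | 77–99% | 97–100% | 84–97% |
| 0.2, 0.1 | 6.9 h | 59–88% | 88–99% | 99–100% |

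Across these profiles, one sample lies between about 56% and 100% of the peak, depending on the window drawn and the shape of the profile. One arm receives a 2-hour infusion and the others oral doses. The shape may therefore differ by arm, and the shortfall need not cancel in a comparison.

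**The case against.** The best defence is that the two-stage sentence was meant for plasma. It never mentions CSF, it restricts itself to patients with a full curve, and plasma is the only fluid sampled intensively. Randomising CSF times over three windows is also a sensible design for building a group-level profile, and the protocol already plans a population model with Cmax and AUC0-24h as exposure variables. The article refers to a pre-specified analysis plan, which could hold the details.

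Much of this stands. The data would support pooled or population estimates of CSF exposure, and the day-14 samples could inform such a model. It does not remove the point. If the sentence covers CSF, it excludes every CSF observation. If it covers plasma only, two primary endpoints have no stated primary method, because the population model is assigned to a secondary question. An analysis plan could fill a silence. Here the primary analysis section lists Cmax and AUC0-24 without distinguishing the fluids and prescribes one method for them.

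A reader might go further and infer that CSF exposure cannot be estimated at all, or that three quarters of the CSF AUC is unobserved. The documents support neither. Group-level estimation is possible, and 75% is a share of clock time, which says nothing direct about the share of the area. The gap after 8 h is not peculiar to CSF, since intensive plasma sampling also ends at 8 h. Nor does the protocol say that the single concentration will be reported as Cmax, so the shortfall in step 5 is only a risk if someone does so.

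**Conclusion.** The point holds for the stated method. By the two-stage calculation as written, no participant yields a CSF Cmax or a CSF AUC0-24h, although both are primary. This follows from counting scheduled samples and rests on no distributional assumption. It does assume that no serial CSF sampling is planned beyond what the article describes.

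The fault lies in the pairing of endpoint and method; the sampling schedule can stay as it is. The published power figure is sound for log Cmax but is not shown for CSF. The window-level power and the 56–100% range depend on the assumptions stated with them and serve only as a guide to scale.

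**What to change.** Limit the two-stage statement to plasma. For CSF, choose one of these before the data are analysed:

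- **(a)** Name a joint plasma-CSF population model as the primary method for CSF Cmax and AUC0-24h. Use the day-2 samples and whatever day-14 samples are obtained, and label 8–24 h as model-extrapolated.
- **(b)** Redefine the primary CSF endpoint as log CSF rifampicin concentration at 2–8 h post dose on day 2, compared between arms with adjustment for time after dose.

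In either case, state that the power in the Sample size section is for log Cmax and was not shown for the CSF quantity chosen.

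The cost is revised endpoint and analysis wording and some modelling work. The CSF conclusion becomes model-based under (a), or a statement about a concentration instead of a peak or area under (b). No extra lumbar puncture or participant is needed.
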